### 6.2.4 Process for restarting vaccination

The vaccination of a group may be put on hold. Continued vaccination of that group may restart only if AMANET expressly gives authorisation to the Principal Investigator to a resumption of vaccination.

### 6.2.5 Process for stopping vaccination of a group or of the trial

In the event that vaccination of a particular group is stopped, the Sponsor will inform the IEC/IRB through the investigator. A report will be written detailing the rationale used for reaching this decision.

## 6.3 Safety Data Collection and Management Procedures

### 6.3.1 Expected Adverse Vaccine Reactions

As for any adjuvanted vaccine, local reactions are expected. Systemic reactions are less often observed; however, a standardized data collection of adverse reactions will be organized.

So far, clinical experience with aluminium hydroxide has shown that the most frequent local reactions are pain, induration, erythema, swelling at the site of injection. Those reactions are usually mild and transient. There is a lack of information concerning the expected systemic reactions; therefore, a special attention will be given to general signs, i.e. fever, irritability or fussiness, drowsiness, and loss of appetite.

In case of a severe local skin reaction, uni-lateral or contra-lateral, a skin biopsy may be needed as part of the clinical evaluation.

[figure not shown]

### 6.3.2 Safety Data Collection

All the Adverse Events, whether observed by the Clinical Investigator or by the parent/guardian of the participant, will be carefully and accurately documented in the CRF by the Clinical Investigator. For each event/reaction the following details will be recorded:

1. Description of the event(s)/reaction(s),
2. Date and time of occurrence,
3. Duration,
4. Intensity,
5. Relationship with the vaccine,
6. Action taken, including treatment,
7. Outcome.

Safety assessments will be obtained and recorded by the Investigator. He/She will not know which vaccine formulation the subject has received. "Solicited" and "unsolicited" reactions/events will be actively followed during 30 minutes after each injection, and during the following 14 days. The table below summarizes the solicited local and systemic reactions that will be sought after and how intensity will be graded.

**Summary table for solicited local and systemic events with grading system**

| Adverse Event                 | Intensity grade | Parameter                                                                                                 |
|-------------------------------|-----------------|-----------------------------------------------------------------------------------------------------------|
| Pain at injection site        | 0               | Absent                                                                                                    |
|                               | 1               | Minor reaction to touch                                                                                   |
|                               | 2               | Cries/protests on touch                                                                                   |
|                               | 3               | Cries when limb is moved/spontaneously painful                                                            |
| Swelling at injection site*   |                 | Record greatest surface diameter in mm                                                                    |
| Induration at injection site* |                 | Record greatest surface diameter in mm                                                                    |
| Erythema at injection site*   |                 | Record greatest surface diameter in mm                                                                    |
| Contra-lateral reaction*      |                 | Record greatest surface diameter in mm                                                                    |
| Pruritus at injection site    | 0               | Absent                                                                                                    |
|                               | 1               | Easily tolerated by the subject, causing minimal discomfort and not interfering with everyday activities. |
|                               | 2               | Sufficiently discomforting to interfere with normal everyday activities.                                  |
|                               | 3               | Prevents normal, everyday activities.                                                                     |
| Fever                         | 0               | Tympanic temperature < 38°C                                                                               |
|                               | 1               | 38≤ and <38.5 °C                                                                                          |
|                               | 2               | 38.5≤ and <39 °C                                                                                          |
|                               | 3               | > 39 °C                                                                                                   |
| Irritability/Fussiness        | 0               | Behavior as usual                                                                                         |
|                               | 1               | Crying more than usual/ no effect on normal activity                                                      |
|                               | 2               | Crying more than usual/ interferes with normal activity                                                   |
|                               | 3               | Crying that cannot be comforted/ prevents normal activity                                                 |
| Drowsiness                    | 0               | Behavior as usual                                                                                         |
|                               | 1               | Drowsiness easily tolerated                                                                               |
|                               | 2               | Drowsiness that interferes with normal activity                                                           |
|                               | 3               | Drowsiness that prevents normal activity                                                                  |
| Loss of appetite              | 0               | Appetite as usual                                                                                         |
|                               | 1               | Eating less than usual/ no effect on normal activity                                                      |

[figure not shown]

|           |   |                                                         |
|-----------|---|---------------------------------------------------------|
| Diarrhoea | 2 | Eating less than usual/ interferes with normal activity |
|           | 3 | Not eating at all                                       |
|           | 0 | None                                                    |
|           | 1 | More than usual, but no dehydration                     |
|           | 2 | With some dehydration                                   |
|           | 3 | With severe dehydration                                 |

The maximum intensity of local injection site swelling, induration and erythema will be scored as follows:

- 0 None
- 1 < 25 mm
- 2 25≤ and <50 mm
- 3 ≥ 50 mm

Reports of all reactions will be investigated and documented in the source record. Local symptoms will be ranked as mild (grade 1), moderate (grade 2) or severe (grade 3) by the size of the reaction as summarised above.

### 6.3.3 Time period, frequency, and method of detecting adverse events and serious adverse events

All AEs occurring within one month following administration of each dose of vaccine must be recorded on the Adverse Event form in the subject's CRF, irrespective of severity or whether or not they are considered vaccination-related.

Additionally, in order to fulfil international reporting obligations, SAEs that are related to study participation (e.g. procedures, invasive tests, a change from existing therapy) or are related to a concurrent medication will be collected and recorded from the time the subject consents to participate in the study until she/he is discharged.

The investigator will inquire about the occurrence of AEs at every visit/contact during the study and throughout the follow-up phase as appropriate.

All AEs either observed by the investigator or one of his clinical collaborators or reported by the participant's parent/guardians spontaneously or in response to a direct question will be evaluated by the investigator. AEs occurring within one month following administration of each dose of vaccine not previously documented in the study will be recorded in the Adverse Event form within the subject's CRF. The nature of each event, date and time (where appropriate) of onset, outcome, intensity and relationship to vaccination should be established. Details of any corrective treatment should be recorded on the appropriate page of the CRF.

As a consistent method of soliciting AEs, the subject will be asked non-leading questions such as:

*"Have you felt different in any way since receiving the vaccine or since the previous visit?"*

AEs already documented in the CRF, i.e. at a previous assessment, and designated as "not recovered/not resolved" or "recovering/resolving" should be reviewed at subsequent visits, as necessary. If these have resolved, the documentation in the CRF should be completed.

**Note: If an AE changes in frequency or intensity during the specified reporting period, a new record of the event should be entered.**

[figure not shown]

When an AE/SAE occurs, it is the responsibility of the investigator to review all documentation (e.g., hospital progress notes, laboratory, and diagnostics reports) relative to the event. The investigator will then record all relevant information regarding an AE/SAE on the CRF or SAE Report Form as applicable. It is not acceptable for the investigator to send photocopies of the subject's medical records to AMANET in lieu of the appropriate completed AE/SAE pages. However, there may be instances when copies of medical records for certain cases are requested by AMANET. In such an instance, all participant identifiers will be blinded on the copies of the medical records prior to submission to AMANET.

The investigator will attempt to establish a diagnosis of the event based on signs, symptoms, and/or other clinical information. In such cases, the diagnosis should be documented as the AE/SAE and not the individual signs/symptoms.

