| Serology Schedule             | D0, D28, D56, D84, and D365                                                                                                                                                                                                                                                                                                                                                                                                                                                                                                                                                                                                                                                                                                                                                                                                                                                                                                                                                                                                                                         |
| Primary Evaluation Criteria   | 
The safety profile will be assessed on the following criteria:
 
 
- Immediate reactogenicity (reactions within 30 minutes after each injection, with emphasis on allergic reaction).
 
- Local and systemic reactogenicity measured from Day 0 to Day 14 after each dose.
 
- Any adverse event resulting in a visit to a physician between each injection and one month after the third dose.
 
- Any Serious Adverse Event (SAE) occurring from inclusion and through out the study. The relationship of the adverse event to the study vaccine will be established by the investigator, using the following definitions : related, or not related
 
- Biological safety: one month after each vaccination, in reference with the baseline before the first dose, by measuring the following: 
 
▪ RBC, haemoglobin, haematocrit, platelets, and WBC.
 
▪ ASAT, ALAT, total bilirubin, alkaline phosphatase, creatinine.
 
 
 
 |

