## 2 OBJECTIVES

### 2.1 Primary Objective

**To evaluate the safety and reactogenicity** of three doses of 30 and 100µg GMZ2, adsorbed on aluminium hydroxide, in comparison with three doses of the control vaccine (rabies), in healthy Gabonese children aged 1-5 years. This will be done through evaluation of the following:

1. Immediate reactogenicity; defined as any systemic adverse reactions occurring within 30 minutes after each injection,
2. Local and systemic reactogenicity measured from Day 0 to Day 14 after each dose,
3. Any unsolicited Adverse Event resulting in a visit to a physician between each injection and one month after the third dose,
4. Any Serious Adverse Event (SAE) occurring from the inclusion throughout the study.

Biological safety, one month after each vaccination, in reference with the baseline level the following :

1. RBC, haemoglobin, haematocrit, platelets and WBCs
2. Creatinine, ASAT, ALAT, total bilirubin and alkaline phosphatase.

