#### 3.1 Overview

- Randomized, controlled, double-blind phase I study
- One trial centre
- Safety oversight by a Safety Committee
- Study monitoring by AMANET
- Screening will be done within 14 days prior to the first vaccination
- Vaccination schedule will be on study days 0, 28 +/- 3, and 56 +/- 3
- Route of administration will be intramuscular on the deltoid muscle, alternately starting with the left side.
- Study duration will be approximately 13 months per participant
- Each participant will attend 16 standardised visits at the trial centre (Inclusion visit D-14; D0; D1; D3; D7; D14; D28; D29; D31; D35; D42; D56; D57, D70, D84, D365).
- Blood samples will be taken by venopuncture at five time points at D-14; D0; D28; D56; D84, and D365. Biological parameters and serological will be assessed at these time points as well as serological parameters. A maximum total of 7.5 mL blood will be taken at each blood sampling. For each participant a maximum of about 37.5 mL blood will be taken during the whole study.
- Twenty four hours, 3 days, 7 days and 14 days after each vaccination a visit is planned to monitor adverse events at D1, D3, D7, D14, D29, D31, D35, D42, D56, D57, D 59, D63 and D70
- Follow-up of serious adverse events (SAEs) until resolution
- The primary analysis will be conducted for all primary and secondary endpoints at a data-lock-point one month post vaccination 3 (study Day 84), after which the Primary

[figure not shown]

Study Report will be produced. These results will be used to decide on the go criteria for the next trial in children.

- The study will then continue in a single-blind fashion. Data gathered during this period will be reported in an addendum report.
- At the end of the study participants will be informed which vaccine they received and those who received malaria vaccine will be offered immunization with the rabies vaccine.

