### **6.3.9 Post study adverse events and serious adverse events**

A post-study AE/SAE is defined as any event that occurs outside of the AE/SAE detection period defined earlier in this Section. Investigators are not obligated to actively seek AEs or SAEs in former study participants.

However, if the investigator learns of any SAE, including a death, at any time after a subject has been discharged from the study, and he/she considers the event reasonably related to the investigational product, the investigator will promptly notify the Study Contact for Reporting SAEs.

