## 7 EVALUATION CRITERIA

### 7.1 Primary Evaluation Criterion: Safety

#### 7.1.1 Definition of the Criterion

The safety profile will be assessed on the following criteria:

- Immediate reactogenicity (reactions within 30 minutes after each injection),
- Local and systemic reactogenicity measured from Day 0 to Day 14 after each dose
- Any unsolicited adverse event resulting in a visit to a physician between each injection and one month after the third dose.
- Any Serious Adverse Event (SAE) occurring from the inclusion through out the study. The relationship of the adverse event to the study vaccine will be established by the investigator, using the following definitions: related or not related.
- Biological safety, one month after each vaccination, in reference with the baseline before the first dose, by measuring the following:
  - RBC, haemoglobin, haematocrit, platelets, total WBC;
  - serum creatinine, ASAT, ALAT, total bilirubin, alkaline phosphatase.

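### Beyond one month after a dose, section 6.3.3 provides only for SAEs judged related to study participation or a concurrent medication, which contradicts the primary criterion of any SAE throughout the study

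*Protocol*

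**What the plan says.** **The criterion.** Protocol 2.1 lists among the components of the primary objective "Any Serious Adverse Event (SAE) occurring from the inclusion throughout the study". Section 7.1.1 repeats it ("Any Serious Adverse Event (SAE) occurring from the inclusion through out the study"), as does the Synopsis ("Any Serious Adverse Event (SAE) occurring from inclusion and through out the study"). In 7.1.1 and the Synopsis the investigator then labels each event related or not related, so both kinds are expected in the data.

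**The recording rule.** Section 6.3.3 carries the title for the period, frequency and method of detecting AEs and SAEs. It gives two windows:

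- "All AEs occurring within one month following administration of each dose of vaccine must be recorded on the Adverse Event form", whatever their severity or relationship to vaccination.
- In addition, over the longer span between consent and discharge, "SAEs that are related to study participation (e.g. procedures, invasive tests, a change from existing therapy) or are related to a concurrent medication".

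**Text that depends on the rule or resembles it.** Section 6.3.9 defines a post-study AE or SAE as "any event that occurs outside of the AE/SAE detection period defined earlier in this Section". Section 7.1.3 C asks for unsolicited events from visits 2 to 17 to be documented, and for those that are serious to be handled as SAEs. Visit 2 is Day 0 and visit 17 is Day 84.

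**Text that points the other way.** Under 6.2.1 the Local Safety Monitor receives all SAEs. Under 6.2.2 the DSMB is told of SAEs during the study whatever their relationship to the vaccine. Section 6.3.6 classifies the outcome of any SAE reported over the entire study. Section 6.3.8 has the investigator report all SAEs to the sponsor. The home visits on Days 140, 224 and 308 (section 5.3) record adverse events since the last contact, and the flow chart marks SAEs at Day 365.

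**The concern.** A primary safety criterion of any SAE needs a recording rule that takes in every SAE first and judges causality second. Section 6.3.3 reverses that order outside the one-month windows: an event qualifies only once it has been judged related to participation or to a concurrent medication. An SAE judged unrelated in the long follow-up, or between consent and the first dose, fits neither window.

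The practical consequence is that an unrecorded event cannot be looked at again. Section 6.3.4 lets the investigator revise a causality opinion as information arrives, but that presupposes a form to amend. The listed examples of participation-related SAEs (procedures, tests, changes of therapy) also do not name the vaccine, so even a late vaccine-related SAE is covered only if participation is read broadly.

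**Working it through.** The protocol gives no figure to reproduce here. The check sets the windows against the criterion and then does day arithmetic.

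**Coverage of an SAE judged unrelated to vaccine, participation and concurrent medication**

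| Period | Criterion (Synopsis, 2.1, 7.1.1) | 6.3.3, one-month window | 6.3.3, consent-to-discharge window | 7.1.3 C (visits 2–17) |
|---|---|---|---|---|
| Consent to dose 1 | counted | no | no | no |
| Day 0 to Day 84 | counted | yes | no | yes |
| About Day 86 to Day 365 | counted | no | no | no |

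The first row takes inclusion to be the Day −14 visit, which is how 3.1 labels it. If inclusion meant the day of first vaccination, that row would drop out and the third would remain.

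**Inputs.** Doses on Days 0, 28 and 56; last visit on Day 365 (Synopsis). One month taken as 30 days, the figure used in 6.3.6.

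**Length of the late gap**

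- End of the all-event window = day of dose 3 + one month = 56 + 30 = Day 86.
- Uncovered days = 365 − 86 = 279.
- Share of follow-up = 279 / 365 = 76%.

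**Sensitivity**

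- One month as 28 to 31 days: the window ends on Day 84 to 87, leaving 281 to 278 days (77% to 76%).
- Dose 3 on Day 50 to 62 and last visit on Day 351 to 379, with a 30-day month: from 259 / 351 = 74% to 299 / 379 = 79%.

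**Possible number of events.** The protocol gives no SAE rate for these children. As an assumption only, take 0.05 to 0.30 unrelated SAEs per child-year in 30 children:

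- 30 × 0.05 × 279 / 365 = 1.1
- 30 × 0.30 × 279 / 365 = 6.9

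So about 1 to 7 events in the trial would fall in the gap. With 10 children per arm (8.2), one child with an unrecorded event changes an arm's proportion by 1 / 10 = 10 percentage points.

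**Which analysis is touched.** Section 3.1 locks the primary analysis at Day 84, and later data go into an addendum. The late gap starts at about Day 86, so it lies wholly in the addendum. The hypothesis in 8.6.1 concerns serious adverse reactions, so SAEs judged unrelated do not enter that test; they enter the descriptive any-SAE criterion.

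**The case against.** The strongest reply is that 6.3.3 limits nothing. Its second sentence opens with *Additionally* and never says *only*. The same section has the investigator ask about AEs at every contact through follow-up and record the relevant information whenever an AE or SAE occurs. With the duties in 6.2.1, 6.2.2, 6.3.6 and 6.3.8 and the home visits, a site following the whole protocol would capture unrelated SAEs. Most of this stands: the protocol does not show an intention to omit them. It does not remove the defect. The section that fixes the detection period gives the narrower rule, nothing says which text prevails, and the relatedness clause would have no function if all SAEs were already meant. Reporting duties act on events once they are known; they do not set the recording window.

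Several stronger readings are tempting and are not supported:

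- **That the filter would work differently by arm and bias the result towards safety.** Section 3.1 says "The study will then continue in a single-blind fashion" after Day 84, but neither it nor 8.7.1 says who is unblinded. It is therefore unknown whether the person judging causality would know the allocation.
- **That the empty SAE cells at Days 140, 224 and 308 in the flow chart mean SAEs are not collected there.** The field-worker columns are empty in almost every row, including rows for information that section 5.3 requires at home visits.
- **That 6.3.9 releases the investigator from seeking SAEs during follow-up.** Its relief applies to former participants; a child awaiting the Day 365 visit is not one. Only its definition, by reference to the detection period, is out of line.
- **That the five SAEs in the adult trial (1.7.4.2), all judged unrelated to vaccination, show what would be missed.** They were reported and followed up, and vaccine-relatedness is not the test 6.3.3 applies.

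**Conclusion.** This is an internal inconsistency about which SAEs enter a primary safety criterion. Sections 6.3.3 and 7.1.3 C leave out SAEs judged unrelated between consent and dose 1 and from about Day 86 to Day 365. The Synopsis, 2.1 and 7.1.1 count them, and the reporting sections assume they are captured.

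The late gap is about 76% of follow-up days (74% to 79% across the visit windows). That is a share of calendar time, not of events lost. The conclusion assumes that 6.3.3 is read literally and that one month is about 30 days; the pre-dose part also assumes that inclusion is the Day −14 visit. The exposure is confined to the descriptive any-SAE criterion and, for the late part, to the addendum. The documents do not establish that any SAE would be missed, nor a direction of bias.

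**What to change.** - **6.3.3:** state that all SAEs, whatever their relationship to vaccine, procedures or other medication, are recorded and reported from consent to the Day 365 visit, and that causality is classified after recording.
- **6.3.9:** define post-study events as those after the child's discharge from the study.
- **7.1.3 C:** keep the visit 2 to 17 window for non-serious unsolicited events, and refer to 6.3.3 for SAEs.

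This is a change of wording only. No visit is added, because the home visits and the Day 365 visit already provide the contacts. The cost is a few extra forms for unrelated SAEs, about 1 to 7 in the late period under the assumed rates above.
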